### Data collection and monitoring

All data will be recorded by trained clinical investigators in a standardized case report form (CRF) and instantly recorded in the database via the ClinResearch Electronic Data Capture System at http://www.tcmcec.net/crivrs/. To ensure the accuracy and reliability of the data, the study monitor will verify and cross-check the CRFs against the investigator’s source document records and drug-dispensing log. Missing data or specific errors in the data will be detected by programs, and the results will be sent to the investigator for resolution. Except for the treatment code, any individual identification of the subjects will not be released until the database is closed. Written documentation of changes will be available via electronic logs and audit trails. Original CRFs will be kept at the participating center for 5 years after completion of the study. Three committees have been established to guarantee the validity and integrity of the intervention protocols by the multicenter trial coordination group. The first is the clinical trial guidance committee, which is responsible for study design and the implementation process. The second is the data and safety monitoring board, which will monitor the data collection process to control its quality. The third is the outcome evaluation committee, which will evaluate the key outcomes (including outcome measurements and adverse events [AEs]).

### Study procedures

During the treatment, the following information will be collected and recorded: basic medical history, diagnosis and screening, observation of effectiveness, and physicochemical examination. Also, the following data will be recorded at visits 1–6: vital signs, physical examination, merge disease means comorbidity, fasting blood sugar, blood pressure, and AEs. In addition, glycosylated hemoglobin, blood lipids, Michigan Diabetic Neuropathy Score (MDNS), Electrocardiogram (ECG), and liver and kidney function will be assessed at visit 3, and glycosylated hemoglobin, blood lipids, MDNS, ECG, liver and kidney function, and NCV will be added at visit 6. All information related to the treatment schedule is provided in Fig. 2.

**Fig. 2 Fig2:**
[figure not shown]
Treatment schedule. *MDNS* Michigan Diabetic Neuropathy Score

### Ethical issues

This study has been approved by the ethics committee of Guang’anmen Hospital of the China Academy of Chinese Medical Sciences (number 2016-096-KY-01). Each participating center obtained approval from its local institutional review board. All of the study participants will provide written informed consent prior to participation.

### Randomization and allocation

Treatment allocation occurs when the study participant meets the inclusion criteria and signs the informed consent form. The therapist will then register the participant in the database, which in turn asks if the participant is willing to be randomized. After the therapist enters “yes,” the specific randomization program behind the form displays the participant’s group assignment number (placebo versus Chinese medical herb). Specific randomization lists will be computer-generated and concealed from the researchers by a senior data manager not involved in the study. This information will remain confidential and will not be made available to the investigator. The allocation list will be protected by password-accessible files and held by an independent noninvestigator. In the event of a medical emergency, the individual’s randomization code and group allocation can be identified.

### Sample size

According to the preliminary study of TangBi prescription data, the placebo group scale (MDNS) score difference was 3.45 and the TangBi prescription scale score was 4.14, with an SD of 1.33. The sample size was estimated using a hypothesis test formula of measurement data: *N* = 2 × [(Zα + Zβ) × δ/*d*]^2^, where *N* is the sample size and δ is the estimated SD, *d* is two groups’ continuous variable mean difference, and Zα and Zβ are the corresponding standard normal differences. Supposing α = 0.05 and β = 0.10, according to the one-sided check table, the quantile Zα = 1.64485 and Zβ = 0.84162, and these are entered into the formula. It is estimated that a sample size of 78 subjects per group will be required, taking into account 20% dropout and withdrawal. This results in 188 participants in total. Intention-to-treat analysis will be used to minimize bias due to dropouts.

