**Methods/design:**

We are conducting a multicenter, placebo-controlled, double-blind, randomized, controlled clinical trial as a means of assessing the therapeutic effects of traditional Chinese medicine (TCM) treatment. A total of 188 patients will be randomized in a 1:1 ratio to a treatment group (TangBi Formula plus mecobalamin) and a control group (placebo plus mecobalamin). The test period lasts 6 months, during which all of the patients will be given standard medical care as recommended by established guidelines. The primary outcome will be development of differences in changes in clinical symptoms and signs in patients and changes in Michigan Diabetic Neuropathy Score (MDNS) between the two groups before and after treatment. The secondary outcome will be changes in nerve conduction velocity and in single clinical signs and symptoms. Safety assessments and adverse events will also be evaluated.

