### Statistical analysis

Three analysis sets will be used for analyzing data. First is the full analysis set (FAS), which refers to the ideal set of subjects as close as possible to the principle of intentionality analysis (including all of the subjects randomized to enroll and receive at least one treatment). If any given case is missing a main variable, the results of the closest observation are carried forward to the absence of the test data. The number of subjects evaluated at the end of each group is kept as consistent as possible before the start of the study. Second is the per-protocol set (PPS), in which all of the factors are in accordance with the research plan; patients show good compliance, using 80–120% of the prescribed dose; the CRF contains the details of the case; and the main variables can be determined. All of the baseline variables must be available, and there must be no major violation of the test plan. Third is the safety analysis set (SS), in which all of the subjects must receive at least one treatment after randomization.

Demographic and other baseline characteristics and efficacy analysis are set as the FAS and PPS. Safety analysis procedures are set as the SS. Data will be collected and analyzed using SAS 9.3 software (SAS Institute, Cary, NC, USA), and statistical analysis will be completed by the third-party personnel statisticians. All of the statistical tests are two-sided, and statistical significance is set at *P* ≤ 0.05.

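### 188 randomised patients do not leave 78 per group after 20% dropout: the allowance appears to have been multiplied by 1.2 instead of divided by 0.8

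*Protocol article*

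**What the plan says.** The Sample size section of the protocol article takes its planning values from earlier data: "the placebo group scale (MDNS) score difference was 3.45 and the TangBi prescription scale score was 4.14, with an SD of 1.33". The stated error rates are "Supposing α = 0.05 and β = 0.10". From these it concludes that "78 subjects per group will be required, taking into account 20% dropout and withdrawal. This results in 188 participants in total".

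The Abstract (Methods/design) repeats the total: "A total of 188 patients will be randomized in a 1:1 ratio". That means 94 per group.

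The step from 78 per group to 188 in total is not written out. The Statistical analysis section states that "All of the statistical tests are two-sided", and it runs the efficacy analysis on both the full analysis set and the per-protocol set.

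**The concern.** A dropout allowance is meant to ensure that the required number of patients is still evaluable after the expected loss. The loss is a fraction of those randomised, so the required number has to be divided by one minus the dropout rate. Adding 20% of the required number gives too few, because 20% of the larger, randomised number is then lost.

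The total of 188 looks like the result of adding 20%. If so, the article claims a tolerance for loss that its sample size does not have, and later reports may repeat the claim.

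The wording adds a second difficulty. Grammatically, the dropout clause attaches to the 78, so a reader could take 78 as the number after inflation.

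**Working it through.** **Inputs** (Sample size section unless noted): required number 78 per group; dropout 20%; total 188; 1:1 allocation (Abstract); difference in mean MDNS change d = 4.14 − 3.45 = 0.69; SD = 1.33; α = 0.05; β = 0.10; two-sided testing (Statistical analysis section).

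**1. Where 78 comes from.** The article's formula is n per group = 2 × [(Zα + Zβ) × SD / d]², with SD / d = 1.33 / 0.69 = 1.9275.

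| Setting | Zα + Zβ | n per group |
|---|---|---|
| Two-sided 5%, 90% power | 1.9600 + 1.2816 | 78.08 |
| One-sided 5%, 90% power | 1.6449 + 1.2816 | 63.6 |
| Quantiles as printed | 1.64485 + 0.84162 | 45.9 |

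Only the two-sided, 90%-power setting gives 78, and it does so with no dropout in it. So 78 is the number before inflation. (Strict rounding up of 78.08 would give 79; the plan's own 78 is used below.)

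**2. Reproducing 188.** 78 × (1 + 0.20) = 93.6, rounded up to 94 per group; 2 × 94 = 188. This matches exactly.

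**3. The allowance that keeps 78.** 78 / (1 − 0.20) = 97.5, rounded up to 98 per group; 2 × 98 = 196. This is 8 more than 188.

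**4. What 188 delivers at 20% loss.** 188 × 0.80 = 150.4, so about 150 in total or 75 per group, which is 3 per group below 78.

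**5. The loss that 188 can absorb.** 1 − 156/188 = 17.0%.

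**6. The other reading of the sentence.** If 78 already included dropout, the total would be 2 × 78 = 156, not 188. That reading fails.

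**7. Effect on power.** For a two-sided 5% test with d = 0.69 and SD = 1.33, the normal approximation is Φ(d / (SD × √(2/n)) − 1.96).

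- n = 78: Φ(3.240 − 1.960) = Φ(1.280) = 90.0%
- n = 75: Φ(3.177 − 1.960) = Φ(1.217) = 88.8%

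With the noncentral t distribution the figures are 89.6% and 88.4%. On either basis the drop is about 1.2 percentage points.

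**The case against.** **The effect is negligible.** Three completers per group and about 1.2 points of power would not change the design. This stands as a statement of size, and no additional patients are proposed. It does not make the three printed figures consistent.

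**Dropouts stay in the full analysis set.** The Sample size section announces an intention-to-treat analysis. The withdrawal section and the Statistical analysis section carry values forward for missing data. Treated dropouts therefore remain, and the full analysis set would number close to 94 per group. This stands as a limit on scope: the 75 describes completer and per-protocol analyses. It does not remove the point. The plan itself chose to inflate for loss, it also analyses efficacy in the per-protocol set, and carrying a value forward does not restore the information lost.

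**The Sample size section describes a one-sided calculation.** It works "according to the one-sided check table" and prints "the quantile Zα = 1.64485 and Zβ = 0.84162". At a one-sided 5% level, 75 per group would have about 94% power, so no power deficit would appear. That is correct, but the printed quantiles yield 46 per group, not 78, and they conflict with β = 0.10 and with the two-sided testing planned later. This is a separate and larger error in the same paragraph. The shortfall here is measured against the 78 the article says it requires, and it holds whichever quantiles are used. Only the power figures depend on the two-sided setting.

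**Multiplying by 1.2 is inferred.** The article does not print the step. The inference fits exactly, and the conclusion does not need it: however 188 was reached, a 20% loss leaves about 75 per group.

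**Conclusion.** The point holds. The figures 78 per group, 20% dropout and 188 in total are mutually inconsistent. At 20% loss, 188 leaves about 75 evaluable patients per group; to keep 78 the total would be 196, and 188 itself covers 17.0% loss.

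The consequence is small: 8 randomised patients, 3 completers per group, and about 1.2 points of power. This rests on three assumptions: the 20% is a proportion of those randomised, loss is equal in the two groups, and power is judged at the plan's difference of 0.69 and SD of 1.33 with a two-sided 5% test. It is an error in a headline design statement that should be corrected, but it does not threaten the trial.

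**What to change.** Keep 188 and correct the Sample size text. State that 78 is the evaluable number per group before any dropout allowance, and then use one of two statements:

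- 188 randomised (94 per group) keeps 78 evaluable per group if loss is no more than about 17%; or
- with 20% loss, 188 randomised leaves about 75 evaluable per group, with two-sided power of about 88% at the planning assumptions.

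In the same edit, reconcile the sidedness and quantiles with 78. Otherwise the 88% would sit beside inputs that do not produce it.

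The cost is wording only. The recruitment target, the randomisation and the analysis do not change; the stated dropout tolerance or power becomes slightly less favourable. According to Trial status, 73 patients had been recruited and none had completed treatment when the manuscript was submitted, so as of that point the correction could be made before any patient's end-of-treatment outcome was known.

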### Bias analysis

The evaluation index of this study is clinical symptoms, affected by many factors. The following factors may affect or bias the results: (1) blood glucose levels, (2) existing treatment measures, and (3) the conditions under which EMG is determined. These influencing factors are addressed as follows. For factors influencing blood glucose levels, a randomized, double-blind study design will be used to ensure consistency across the two groups. Administration of methycobal can reduce the psychological effect on patients and increase patient compliance. EMG specialists should be trained consistently, and the standards for fixed EMG should be established as a standard operating procedure for this study.

### Outcome measurements

#### Primary outcome measures

Changes in clinical signs and symptoms in patients with DSPN: Changes in clinical signs and symptoms will be evaluated prior to treatment and at weeks 12 and 24 of the treatment phase.Changes in the MDNS are compared between the two groups before and after medication. The clinical signs and symptoms of patients will be recorded using the MDNS. MDNS will be evaluated prior to treatment and at weeks 12 and 24 of the treatment period.

#### Secondary outcome measures

Changes in NCV: The changes in NCV of each nerve will be compared before and after administration of medicine. Changes in NCV will be evaluated prior to treatment and at week 24 of the treatment period.

Each center has a designated EMG specialist to ensure the accuracy of EMG reading. Electromyographic detection is to be performed using Neurocare-C electromyography (Neurocare Center Co., Shanghai, China) and evoked potential instruments to determine MCV and SCV of the bilateral median nerve, ulnar nerve, common peroneal nerve, and tibial nerve. The room should be kept quiet, and the temperature should remain at about 25 °C. Skin temperature must remain between 28 °C and 30 °C, and hyperthermic treatment should be provided to patients with low body surface temperature. SCV is determined using the reverse method, which means proximal stimulus and remote reception. The sensory waveform is derived from the average deconvolution by machine automatically. SCV value is the measured distance (between receiving point and the stimulus point)/incubation. MCV is determined in the corresponding distal muscles. The corresponding nerve branch is superstimulated to elicit two action potentials: far end and near end. MCV is the distance between two points/difference in incubation between the two points. The NCV normal value refers to the clinical electromyography standard for the median nerve and ulnar nerve with MCV ≥ 45 m/second and SCV normal values ≥ 47 m/second individually. MCV normal values of peripheral nerve and tibial nerve separately were ≥ 42 m/second and ≥ 40 m/second. Values below those stipulated above indicate that NCV has slowed down, that means NCV abnomal.2.Changes in clinical signs and symptoms: The clinical symptoms and signs of the patients will be compared before and after taking the medicine and will be evaluated prior to treatment and at weeks 12 and 24 of the treatment phase.

### Safety assessment and adverse events

Safety will be monitored for 6 months after the intervention and evaluated on the basis of the incidence of AEs, including clinically significant changes in physical examinations, vital signs, and standard clinical laboratory tests. Vital signs include body temperature, blood pressure, respiration, heart rate, and similar factors at months 0–6 Routine blood examination, routine urinalysis, and routine stool examination will be done at months 0, 3, and 6. ECG, five items assessing liver function (alanine aminotransferase, aspartate aminotransferase, γ-glutamyl transpeptidase, alkaline phosphatase, and total bilirubin), renal function (blood urea nitrogen), and SCr will be measured at months 0, 3, and 6. In addition, we will make at least one on-site monitoring visit during the study to ensure that each participating center complies with the study protocol and GCP principles. AEs, such as signs and symptoms and other ailments, will be documented at every study visit. Each AE will be classified as a mild, moderate, or severe AE, and its correlation with the intervention drugs will be assessed. Severe AEs will be reported to the principal investigator and the ethics committee within 24 h. The data and AEs will be accurately and appropriately recorded on the CRF. All of the AEs will be recorded, monitored, and treated until properly resolved. The schedule of enrollment, interventions, and assessments is presented in Fig. 3.

**Fig. 3 Fig3:**
[figure not shown]
Content for the schedule of enrollment, interventions, and assessments

### Statistical analysis

Three analysis sets will be used for analyzing data. First is the full analysis set (FAS), which refers to the ideal set of subjects as close as possible to the principle of intentionality analysis (including all of the subjects randomized to enroll and receive at least one treatment). If any given case is missing a main variable, the results of the closest observation are carried forward to the absence of the test data. The number of subjects evaluated at the end of each group is kept as consistent as possible before the start of the study. Second is the per-protocol set (PPS), in which all of the factors are in accordance with the research plan; patients show good compliance, using 80–120% of the prescribed dose; the CRF contains the details of the case; and the main variables can be determined. All of the baseline variables must be available, and there must be no major violation of the test plan. Third is the safety analysis set (SS), in which all of the subjects must receive at least one treatment after randomization.

Demographic and other baseline characteristics and efficacy analysis are set as the FAS and PPS. Safety analysis procedures are set as the SS. Data will be collected and analyzed using SAS 9.3 software (SAS Institute, Cary, NC, USA), and statistical analysis will be completed by the third-party personnel statisticians. All of the statistical tests are two-sided, and statistical significance is set at *P* ≤ 0.05.

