### Subjects’ voluntary withdrawal

As stipulated in their informed consent forms, the subjects have the right to withdraw from the study at any time. Participants who do not formally withdraw from the study but cease to accept medication and undergo testing or who become impossible to contact are also considered withdrawn. The researcher should realize and record the reasons for subjects’ withdrawal to the greatest extent possible, noting whether the treatment is obviously ineffective, difficult to tolerate owing to adverse reactions, or whether the patient cannot continue to participate in clinical research for some other reason, such as economic or personal factors. Whatever the reason, the case record should be retained; the last test results will be carried forward to the final result; and a full dataset will be analyzed for the treatment’s efficacy and adverse effects.

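### Carry-forward gives an MDNS change of zero to patients lost before week 12, which can cost substantial power and biases the comparison when early loss differs between arms

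*Protocol article*

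**What the plan says.** The Statistical analysis section of the protocol article defines the full analysis set (FAS) as all randomized subjects with at least one treatment. It does not require a post-baseline assessment. For a missing main variable it states that "the results of the closest observation are carried forward to the absence of the test data". The section on subjects' voluntary withdrawal adds, for anyone who withdraws or is lost to contact, that "the last test results will be carried forward to the final result".

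The assessment times are sparse. Under Primary outcome measures, MDNS is taken before treatment and at weeks 12 and 24. For nerve conduction velocity, Secondary outcome measures states: "Changes in NCV will be evaluated prior to treatment and at week 24 of the treatment period".

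The Effectiveness analysis section compares change from baseline between arms by t test or Wilcoxon rank-sum test. The Sample size section gives the planning figures: "the placebo group scale (MDNS) score difference was 3.45 and the TangBi prescription scale score was 4.14, with an SD of 1.33". It allows 20% for dropout and arrives at 188 participants, which is 94 per arm.

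**The concern.** With only two post-baseline MDNS assessments, the rule fixes the outcome of dropouts mechanically. A patient lost before week 12 has only a baseline score, so the imputed change is exactly 0. A patient lost between weeks 12 and 24 keeps the week-12 score. For a withdrawn subject without a week-24 NCV, the last result is the baseline value, so that change is 0 as well.

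If both arms are expected to improve by several points, zeros lie far from the rest of the data. They shrink the difference between arms and inflate the variance, and the analysis treats them as observed. The 20% sample-size allowance is meant to leave enough real outcomes with SD 1.33, but the FAS rule puts the dropouts back as constructed values. The difference 0.69 and the SD 1.33 then no longer describe the analysed data.

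If early loss differs between arms, the arms receive different shares of zeros and the difference in dropout appears as a difference in effect. The article itself names lack of effect and poor tolerability as possible reasons for withdrawal, and either could differ by arm.

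**Working it through.** **Inputs.** From Sample size: 3.45 (placebo), 4.14 (TangBi), SD 1.33, 20% dropout, 188 in total. From Statistical analysis: "All of the statistical tests are two-sided, and statistical significance is set at" 0.05. Assumed: 3.45 and 4.14 are mean improvements at week 24, and 1.33 is the SD of that change. The article does not give the timing of dropout or the share of the response present at week 12, so both are varied.

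**Reproducing the plan's figure.** n = 2[(Zα + Zβ) × SD/d]², with d = 4.14 − 3.45 = 0.69. Two-sided 5% and 90% power give 2[(1.960 + 1.282) × 1.33/0.69]² = 78.08, which matches the stated 78. Then 78 × 1.2 = 93.6, so 94 per arm and 188 in total. The quantiles printed in the article give 45.9 instead. That is a separate matter and is not used here.

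**Benchmark.** With 20% lost, 94 × 0.8 ≈ 75 per arm are observed. If dropout is unrelated to outcome, two-sided power is about 88%.

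**All 20% lost before week 12.** With share p set to 0, an arm has mean (1 − p)μ and variance (1 − p)SD² + p(1 − p)μ².
- TangBi: mean 0.8 × 4.14 = 3.312; variance 0.8 × 1.7689 + 0.16 × 17.1396 = 4.157.
- Placebo: mean 0.8 × 3.45 = 2.760; variance 0.8 × 1.7689 + 0.16 × 11.9025 = 3.320.
- Difference 0.552; average SD √[(4.157 + 3.320)/2] = 1.93; SE √[(4.157 + 3.320)/94] = 0.282.
- Power: 49.9% by the normal formula, 49.5% by the t test, and about 59% for Wilcoxon by simulation.

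**Other timings.** Let r be the share of the week-24 change present at week 12, and let later dropouts be frozen there (t-test power, total loss 20%).

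| Timing of loss | Difference | r = 0.5 | r = 0.75 | r = 1 |
|---|---|---|---|---|
| All early | 0.552 | 50% | 50% | 50% |
| Half early | (0.8 + 0.1r) × 0.69 | 62% | 68% | 70% |
| All late | (0.8 + 0.2r) × 0.69 | 79% | 90% | 94% |

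The 94% exceeds the benchmark only because imputed values are counted as observed.

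**Smaller amounts of early loss, no other loss.** 5% gives 83% power and 10% gives about 70%.

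**Dependence on the mean change.** Keep the difference at 0.69, SD 1.33 and 20% early loss, and vary the placebo mean change. Power is 88% at 0, 82% at 1.0, 70% at 2.0 and about 50% at 3.45.

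**Unequal early loss, no true effect (both means 3.45).**
- TangBi 15%, placebo 25%: 0.85 × 3.45 − 0.75 × 3.45 = 0.345, half of 0.69. Variances are 3.021 and 3.558, so SE = √(6.579/94) = 0.265. The test rejects in about 25% of trials, almost always in favour of TangBi.
- With the percentages swapped, the difference is −0.345 and the rejections favour placebo.
- Equal loss of 20%: difference 0 and rejection 5%.

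**Unequal early loss, planned effect present.** TangBi 20%, placebo 10%: 0.8 × 4.14 − 0.9 × 3.45 = 0.207. The placebo variance is 0.9 × 1.7689 + 0.09 × 11.9025 = 2.663, so SE = √[(4.157 + 2.663)/94] = 0.269 and power is about 12%.

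The article gives no planning figures for NCV, so the effect there cannot be sized.

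**The case against.** The strongest objection concerns size. A reader might infer that the trial will have only 50% power. The article does not support that: the figure needs the whole 20% allowance to be lost, all of it before week 12, and a t test. Timing is not stated, the rank-sum test is also allowed and loses less, and all-late loss costs little or nothing. The size also rests on reading the two pilot figures as changes. The sentence calls the first a score difference and the second a scale score, so this is plausible but not certain, and smaller changes would do much less harm. All of this stands, so only a range can be claimed.

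Three other inferences go too far:
- Every missing NCV does not become a zero change. The FAS rule covers a main variable and NCV is secondary, so only the withdrawal rule reaches it, and only for withdrawn subjects.
- The words for last and closest observation look like two conflicting rules. For a patient who leaves and does not return, the closest earlier value is the last value, so they coincide. Their scopes differ, but no conflict in result is shown for dropouts.
- Carry-forward does not generally produce false efficacy. With equal dropout and no true effect, type I error stays at 5%. If poor tolerability of the herbal product caused more TangBi loss, the bias would run against TangBi.

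It can also be said that a per-protocol analysis is planned. That is true, but this set is selected on compliance and available data, so it does not repair the FAS analysis.

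**Conclusion.** The concern holds in this form. The zero change for FAS patients lost before week 12, the freezing of later dropouts at week 12, and the zero NCV change for withdrawn subjects without a week-24 value follow directly from the stated rules and visit schedule.

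For MDNS, if 3.45 and 4.14 are mean changes with SD 1.33, 20% dropout from 94 per arm puts t-test power anywhere from about 50% to 94% depending on when patients leave, against a benchmark of about 88%. A material loss requires that a sizeable share leaves early or that the week-12 response is well short of the week-24 response.

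Bias requires early loss to differ between arms, and it runs against the arm that loses more. More loss on TangBi hides a benefit; more loss on placebo creates a false one. A gap of 10 percentage points is worth 0.345 points, half the planned effect. The 15% and 25% rates are illustrations, not forecasts. The rule governs the primary comparison, so it should be changed.

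**What to change.** Remove carry-forward from both the Statistical analysis and the voluntary-withdrawal sections. Analyse MDNS change at weeks 12 and 24 in the FAS by a mixed model for repeated measures, adjusted for baseline MDNS, with the week-24 contrast between arms as primary. Add a multiple-imputation sensitivity analysis, reference-based or with a delta shift, that explicitly includes patients with no post-baseline MDNS, because a model of change from baseline holds no outcome information on them. For NCV, use a baseline-adjusted analysis or multiple imputation instead of carrying the baseline value forward.

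The price is reliance on a missing-at-random assumption, which the sensitivity analysis is there to probe, and a little more analysis work. No new data or visits are needed, and the planned SAS software can run it. According to Trial status, 73 patients had been recruited at submission and none had completed treatment. The change could therefore have been made at that stage before any patient had completed treatment; it should in any case be fixed before unblinding.
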